9.4. Rationale for setting the target number of subjects

In order to calculate indices of liver fibrosis, inflammation, fatty liver, 300 cases of liver biopsy or liver resection or 30 cases of healthy cases are required as teacher data. In addition, 100 cases of liver biopsy or hepatectomy cases and 20 cases of healthy cases are required to verify the calculated usefulness of the liver fibrosis, inflammation and fatty index. Since there are 250 cases of liver biopsy cases and 50 cases of hepatectomy cases at the institute, we can easily compare them with 400 cases of pathological diagnosis for a total of 3 institutions. Also, 20 healthy volunteers are planned to be imaged at each facility.

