Liver stiffness measured by Shear wave imaging such as FibroScan, VTQ, SWE, SwSm, SWE_GE is affected by inflammation, jaundice, congestion and the like besides fibrosis [10, 20-22], whereas RTE influences inflammation There are reports that it can evaluate fibrosis without receiving it [23]. Therefore, by simultaneously measuring both, there is a possibility that the extent of inflammation and fibrosis of the liver can be evaluated separately.

On the other hand, steatosis of the liver, a method to obtain it from the attenuation coefficient of ultrasonic wave has been reported in the 1980 's [24-27], FibroScan measures liver hardness and simultaneously determines attenuation coefficient of ultrasonic wave Controlled Attenuation Parameter (CAP) has been installed and its usefulness has been reported [28].

In this issue, SWM, which is Shear wave elastography, and attenuation measurement function have been developed from Hitachi Aloka Medical, Inc. and it has become possible to measure on the same equipment as RTE which is conventional Strain elastography.

Therefore, for liver disease cases subject to liver biopsy or hepatectomy, indexes of hepatic fibrosis, inflammation, fatty liver are calculated using the results of pathological diagnosis as teacher data, using the results of RTE, SWM and attenuation measurement Consider an algorithm to do. In addition, blood collection test, pathological diagnosis, FibroScan, VTQ, SWE, SwSm, SWE_GE and MR Touch are performed, their correlation is evaluated, and its usefulness is examined.

3. Target

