3.1. Target case

Applicable to those who fall under ① or ②.

① Liver disease patient undergoing liver biopsy or liver resection.

② Healthy volunteers.

Serologically or diagnostically diagnosing liver disease can be denied as a healthy individual.

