4.1.1. Overall test outline

- Blood sampling, ultrasound elastography (RTE, SWM, FibroScan, VTQ, SWE, SwSm, SWE_GE), attenuation measurement, MR Touch are performed within 4 months before or after liver biopsy or liver resection.
- Blood is drawn on the same day as ultrasonic elastography and attenuation measurement enforcement.

4.1.2. Target number of subjects and scheduled expected duration.

- Target sample size

Total of 450 cases (400 cases of biopsy or surgical cases, 50 healthy volunteers)

- Registration period

From the approval of the Ethics Committee until March 31, 2017. However, shorten or extend the period as necessary.

- Examination period

From the approval of the ethics committee until the last 3 months after registration of the patient. However, shorten or extend the period as necessary.

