5.2.2. Liver pathology

- Liver biopsy or liver resection pathology specimens are stained with ① HE staining and ② masson trichrome staining.
- Make the slide virtual slide and send it to independent pathology interpretation committee member.
- Independent pathology interpretation committee evaluates fibrosis in accordance with new inuyama classification (complies with METAVIR classification).

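### Section 9.4 counts healthy volunteers without histology in both the teacher and verification sets, so pooled results are likely to overstate performance in patients

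*Protocol*

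**What the plan says.** Protocol 2.1 says the indices are derived "using the results of pathological diagnosis as teacher data". Section 9.2 likewise builds them from the association of pathological diagnosis with RTE, SWM and attenuation. Section 5.2.2 describes only one source of pathology: "Liver biopsy or liver resection pathology specimens are stained", with an independent committee reading the slides.

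Section 3.1 admits healthy volunteers as a second target group on this basis: "Serologically or diagnostically diagnosing liver disease can be denied as a healthy individual". No biopsy or other histology is planned for them.

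Section 9.4 then fixes the make-up of the two data sets. For development, "300 cases of liver biopsy or liver resection or 30 cases of healthy cases are required as teacher data". For verification, "100 cases of liver biopsy or hepatectomy cases and 20 cases of healthy cases are required to verify the calculated usefulness". The overall target in 4.1.2 is "Total of 450 cases (400 cases of biopsy or surgical cases, 50 healthy volunteers").

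The stated purpose (0.2 and section 1) concerns liver disease patients having biopsy or resection. The only breakdown promised in 9.2 and 9.3 is by disease.

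**The concern.** A case can act as teacher or verification data only if it has a reference value. For patients that value is read from a slide. For volunteers it would have to be assumed, and the protocol does not say what fibrosis, inflammation or fat grade they receive, or whether headline results will be given for patients alone. A second, unstated reference standard therefore enters both development and verification.

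The likely consequence is a spectrum effect. Pearson correlation, the method named in 9.3, depends on the spread of cases. Adding a block of people at the normal end widens that spread and can raise the coefficient, and any discrimination measure, with no better separation of stages among patients. The verification result is what a reader will use to judge whether the index works in people who would otherwise have a biopsy.

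**Working it through.** **1. The plan's own figures.** 300 + 100 = 400 patients and 30 + 20 = 50 volunteers, total 450. This agrees with 4.1.2, but only if the second *or* in the teacher-data sentence is read as *and*. The volunteers are thus part of the sample-size rationale and not an incidental extra. (Section 9.4 also says "20 healthy volunteers are planned to be imaged at each facility" and refers to "400 cases of pathological diagnosis for a total of 3 institutions"; 20 × 3 = 60 does not match 50 and should be reconciled.)

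**2. Share of volunteers.**
- Teacher set: 30/330 = 9.1%.
- Verification set: 20/120 = 16.7%.
- If labelled F0, their share of the F0 group in verification depends on the patient F0 share (assumed): 20/(20+35) = 36% if 35 of 100 patients are F0, 20/(20+20) = 50% if 20 are, 20/(20+5) = 80% if 5 are.

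**3. Effect of pooling on the correlation.** The protocol gives no stage distribution, variance or expected correlation, so everything in this step is an assumption:
- The index is linear in stage F0–F4, with a patient correlation of r = 0.60.
- Three stage mixes (F0 to F4): even (20% each), few F0 (5/30/30/20/15%), many F0 (35/25/15/10/15%).
- Volunteers have grade 0, an index mean d residual SDs below that of patients' F0, and a residual SD k times the patients'.

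With m and V the mean and variance of stage in patients, σ² = V(1/r² − 1) and w = 20/120:

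- Var(stage) = (1−w)V + w(1−w)m²
- Cov = (1−w)V + w(1−w)·m·(m + dσ)
- Var(index) = (1−w)(V + σ²) + w·k²σ² + w(1−w)(m + dσ)²
- pooled r = Cov / √[Var(stage) × Var(index)]

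Many F0, d = 0, k = 1: m = 1.45, V = 2.0475, σ² = 3.64. Var(stage) = Cov = 1.998, Var(index) = 5.638, so r = 1.998/√(1.998 × 5.638) = 0.595.

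Few F0, d = 1, k = 1: m = 2.10, V = 1.29, σ² = 2.293. Var(stage) = 1.6875, Cov = 2.129, Var(index) = 5.183, so r = 2.129/√(1.6875 × 5.183) = 0.72.

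| Stage mix | Patients only | d = 0, k = 1 | d = 1, k = 1 | d = 1, k = 0.5 |
|---|---|---|---|---|
| Many F0 | 0.60 | 0.595 | 0.64 | 0.66 |
| Even | 0.60 | 0.62 | 0.68 | 0.70 |
| Few F0 | 0.60 | 0.65 | 0.72 | 0.74 |

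Simulation of the same settings agrees to within 0.002 (0.594 at the low end). With equal noise (k = 1) the range is therefore about 0.59 to 0.72. The 0.74 needs volunteers with half the patients' noise, for which the protocol gives no basis.

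**4. Discrimination.** The protocol does not name AUROC; it serves here only as an illustration. For F2 or higher under the same equal-noise settings it moves from 0.79–0.82 in patients to 0.82–0.86 pooled.

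**5. Precision lost by using patients only.** Fisher z at r = 0.60: z = 0.693, SE = 1/√(n−3).
- n = 100: 0.693 ± 1.96 × 0.102, which gives 0.46 to 0.71.
- n = 120: 0.693 ± 1.96 × 0.092, which gives 0.47 to 0.70.

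**The case against.** Sections 9.2 and 9.3 speak of association with pathological diagnosis. Read literally, a case without pathology cannot enter those analyses, and details of grading and display may sit in an analysis plan that is not shown. Results by disease would in effect be patient-only. Including a normal anchor when training an index is also a defensible choice.

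Part of this stands. The grading and pooling are inferred, not stated. But 9.4 itself assigns volunteers to both sets and builds the sample size on them, so this is a stated composition and not a missing detail. Sub-analysis by disease does not make the headline verification patient-only.

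The point about training stands more firmly. If 10% to 20% of patients are F0 (assumed), 300 patients supply 30 to 60 F0 cases, and 30 volunteers would be 30/60 = 50% to 30/90 = 33% of that group. Resections for metastatic disease might supply normal-end histology, since 5.1.1 records the purpose of hepatectomy, but the protocol gives no number for them. A reader might infer that volunteers must be barred from training; the documents do not support going that far.

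Two other stronger readings are tempting. One is that pooling certainly inflates every result; the many-F0 case with d = 0 and k = 1 shows no inflation of r. The other is that some volunteers will carry wrong steatosis labels because serology misses fatty liver. Section 3.1 also allows a diagnostic route, which may include imaging, and the protocol gives no prevalence, so no count of wrong labels can be supported.

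**Conclusion.** The concern holds in a limited form. It is certain from the text that 50 people without the reference standard are counted in the development and verification sets, with no stated grade and no commitment to patient-only headline results. It is likely, but conditional on grade zero and pooling, that pooled figures will overstate performance in patients. The range of about 0.59 to 0.72 for a patient correlation of 0.60 rests on the assumed linear index, stage mixes, volunteer offset and equal noise; it illustrates direction and plausible size and is not an estimate for this study.

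This should be settled before analysis, but it does not undermine the design: all 100 verification patients with histology are planned for in any case, so patient-only results remain available.

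**What to change.** In 9.3 and 9.4, state that the primary verification of the index and its correlation with pathology use the 100 verification cases with histology. Report volunteers separately as a normal range for RTE, SWM and attenuation. Show any pooled result only as a labelled secondary analysis, with the grade assumed for volunteers stated.

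If volunteers stay in the teacher set, state their assumed fibrosis, inflammation and steatosis grades in 9.2 or 9.4, and show the index refitted on the 300 histology cases alone as a sensitivity analysis. While editing 9.4, replace the ambiguous *or* and reconcile 20 volunteers per facility at three institutions with the total of 50.

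The cost is wording and one extra model fit. Enrolment is unchanged. The downsides are a possibly lower headline figure and the slightly wider interval shown above.

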9.5. Exploratory analysis by accompanying research

In the case of newly subordinate research using the data of this study, we summarize the contents to be studied and submit it to this research leader. The research leader will examine the content and implementation method of the incidental research that was proposed together with the proposer.

10. Ethics

All researchers involved in this examination received the Helsinki Declaration and the Ministry of Health, Labor and Welfare's "Ethics Guidelines on Clinical Studies"(http://www.mhlw.go.jp/stf/seisakunitsuite/bunya/hokabunya/kenkyujigyou/i--kenkyu/index.html) and carry out this test.

10.1. Informed consent

10.1.1. Acquisition of explanation and consent to the patient

Before the patient participates in the exam, the attending physician hands out the explanatory document approved by the institutional ethics review committee (or the Institutional Review Board, IRB) to the patient orally and fully. After explaining the test, give enough time to judge as an opportunity to ask a question, ask the patient to understand the contents of the exam well, ask the participation in the exam, depending on the individual's willingness to do so Consent shall be obtained with consent form.

In addition to the physician in charge who explained the explanation, in the consent form, when the test cooperator makes a supplementary explanation, the relevant test cooperator has written, signed or signed the respective date, respectively, and the subject Please fill in the consent date and stamp or sign and sign. A copy of the consent form is provided to the subjects, and the original is preserved in the facility.

10.1.2. Continuous participation in the examination When information possibly affecting the intention of the subject is obtained

(1) If the subject physician got information that may influence the intention of the subject concerning continued participation in the examination while participating in the exam, the attending physician immediately described the information Provide explanatory materials and explain to the subjects the following on the basis.

① About this information

② It is free to continue participation in this exam

(2) In the explanatory document / consent form, the doctor in charge who made the explanation fills in the date of explanation and stamps or signs it, and the examinee fills in the date of receipt of the information and stamps or signs the above name. In addition, if a test cooperator makes a supplementary explanation, the relevant test cooperator also fills in the date and stamps or signs it. A copy of the material shall be provided to the subjects. The attending physician confirms the intention of the subject whether or not to continue participating in this examination, and fills in the intention confirmation date and the confirmation result on the original document of the explanation document / consent form and saves it.

(3) After revising the explanatory document / consent form and obtaining approval from the ethics review committee, the attending physician will explain it again using the revised explanatory document and consent form to the subject, and the participating in this examination For consecutive purposes we obtain written consent from free volunteers from subjects. On that occasion, the doctor in charge fills in the explanation date in the consent form, and stamps or signs it, and the subject also signs and signs or signs after entering the date of consent. A copy of the consent form will be provided to the subject and the original will be stored at the facility.

10.2. Consideration concerning human rights, safety and disadvantage of subjects

10.2.1. Consideration for human rights (protection of privacy)

When dealing with raw data related to the test implementation and agreement form etc, pay close attention to the secrecy protection of the subjects. Also, even in preparation and handling of case report to be submitted outside the hospital, the subject is identified by "case registration number" issued at the time of registration assignment and "subject identification code" set within the facility, and regarding the secret protection consider. Data of subjects obtained in this study will not be used for purposes other than the purpose of this study (if used for purposes other than this research, separate consent will be obtained from the subject as necessary). In addition, when publishing the results of the examination, do not use information that can identify subjects.

10.2.2. Consideration for safety · disadvantage

In the event that any adverse event develops to the subjects participating in the study, the attending physician promptly carries out the necessary response (examination, treatment, discontinuation of examination, etc.) and strives to ensure the safety of the subject.

Liver biopsy or hepatectomy involves various risks, but as shown in 3.1, liver biopsy or hepatectomy is required as part of daily practice irrespective of participation in this study It is targeted at the patient to be judged.

Among the tests added by participating in this study, blood tests and tests using ultrasound such as RTE, SWM, attenuation measurement, FibroScan, VTQ, SWE, SwSm, SWE_GE, or MR Touch, there is no disadvantage.

10.3. Independent Data Monitoring Committee and Kinki University Medical School Ethics Committee Approval

Regarding the implementation of this study, it is approved by the Independent Data Monitoring Committee and the Kinki University Medical School Ethics Committee and the Ehime University Graduate School of Medicine Ethics Committee.

11. Quality control and quality assurance.

11.1. Monitoring

11.1.1. Purpose

Confirm whether the test is performed safely and according to the test implementation plan and whether the data is correctly collected.

11.1.2. Central monitoring (in-house monitoring)

The data center conducts central monitoring with reference to the contents of the case report gathered by the research investigation management staff, RTE, liver biopsy results, with reference to the processing result of the digitized data. No facility visit monitoring is scheduled. Regular monitoring reports prepared by the data center will be submitted to the research representative and the independent data monitoring committee for consideration.

11.1.3. Contents

(1) Eligibility.

(2) Status of case accumulation, especially stop.

(3) Serious adverse events and their reporting status.

(4) Other.

12. Save record

The study responsible doctor keeps the following documents related to the implementation of the test etc. The storage period shall be until 5 years have passed since the publication of research results.

(1) Copy of Application Documents.

(2) Notification document from hospital director.

(3) Applications for various applications and reports of reports.

(4) Subject identification code list.

(5) Record on consent form, consent of subject.

(6) Basic data for preparing case reports (inspection data etc.).

13. Management of personal information and methods of anonymization

The pathological specimen and the ultrasonic examination data are managed by the case registration number given at the completion of registration. Specifically, at the time of case registration, personal identification information corresponding to the specimen is converted into alphanumeric characters, and thereafter, the specimen is treated only with the encoded concatenable anonymization number and used for analysis.

The case and sign reference table shall be kept strictly by the data center, and no clinical information that identifies the individual to the person in charge of the measuring institution will be transmitted.

14. Presentation of research results

- Register for clinical trial registration by the time of starting the study (www.clinicaltrials.gov) and submit it to the English journal after the final analysis is completed. Until the final analysis prescribed by the protocol, no announcement will be made except when approval by the independent data monitoring committee is obtained.
- However, the research representative or the research secretariat can publish the conference · paper (review) for the introduction of the research not including the analysis result of the research end point through the approval of the research representative and the Steering Committee .
- In principle, the author of the main publication of the research results shall be the head of the research secretariat, hereinafter the research representative, RTE, SWM, attendant of attenuation measurement data analysis person, independent pathologist interpreting committee member, statistical analysis director (for publication 1 person in charge at the time of analyzing), but it will decide in consultation with the research representative. Below that, according to the restriction by the contribution regulation of the paper, the faculty research officer is selected for each facility in order of the number of registrations, and it is made a coauthor.
- When writing several different papers, the leader consults with the Steering Committee and emphasizes facilities with a large number of registered cases.
- All coauthors should review the contents of the paper before submission and only those who agree on the content of the presentation. If agreement cannot be obtained in the discussion about contents, the researcher cannot include the researcher as coauthor after acknowledging Steering Committee.
- Because there is a possibility that the conference presentation may be repeated several times, we will announce it by circling from the research secretariat, the research representative, the researcher of the facility where there are many registrations or the doctor of the research execution facility. The presenter will decide the research representative with the approval of the representative group of the research organization. However, at the time of presenting the conference, the Research Secretariat is responsible for preparing the presentation and contents of presentation, and in principle, the Research Secretariat will contact the data center. Presenters other than the research secretariat cannot collect the results of aggregation / analysis directly from the data center without acknowledging the research secretariat and data center.

15. Clinical trial registration

This study is already scheduled to register in ClinicalTrial.gov (www.clinicaltrials.gov) or UMIN Clinical Trials Registry (UMIN - CTR).

16. Conflict of interest and research funding sources

We do not assume any conflict of interest that may affect the planning, implementation and presentation of this exam. Conflict of interest (conflict of interest) refers to interesting relationships that affect research outcomes, including money and personal relationships.

This study supplements research expenditure of GI internal medicine department of Kinki University School of Medicine and conducts research.

Decision making regarding planning, implementation and presentation of this exam is done by the research representative.

17. Response of expense of test participants and health damage

17.1. Expense of Study Participant

Of the tests adopted in this test, RTE, SWM, attenuation measurement, VTQ, SWE, SwSm, SWE_GE, and MR Touch are carried out at the burden of each testing facility because insurance treatment is not approved. Meanwhile, blood tests, liver biopsy or hepatectomy, FibroScan have been approved for medical insurance and are conducted within the scope of routine practice, so RTE, SWM, attenuation measurement, VTQ, SWE, SwSm, SWE_GE, Medical examination expenses including examination other than MR Touch, hospitalization expenses etc. are all paid by patient's insurance and self-payment.

